### Data security/storage

Access to the study database will be restricted and require passwords that are only known to relevant study personnel. Devices used to transport data will be CCF-approved encrypted devices with password protection. Data will be maintained for 6 years after the study’s completion, and HIPAA Privacy and Security Rules will be strictly followed.

### Assessment of safety

Unanticipated problems related to the intervention will be logged and reported to the Institutional Review Board (IRB) at the time of continuing renewal. Major deviations will be reported to the IRB upon discovery.

Periodically during the trial, the study team will:

▪ Review the research protocol▪ Evaluate the trial’s progress▪ Consider external factors, such as scientific or therapeutic developments that may affect the study’s safety or ethics▪ Review center performance, make recommendations, and assist in resolving problems▪ Protect the safety of study participants▪ Conduct interim analysis, if appropriate▪ Ensure confidentiality of trial data and results of monitoring▪ Address any problems with study conduct, enrollment, sample size, or data collection

Any protocol changes that are deemed significant by the investigator team will be reviewed and approved by the IRB at Cleveland Clinic. This will also be shared by AHRQ. All protocol changes will be documented with version control in place.

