## Introduction

### Background and rationale

Community-acquired pneumonia (CAP) is a significant cause of morbidity and mortality, resulting in > 1.7 million adult hospitalizations annually, making it the second most common cause of hospitalization in the USA [1–3]. One contributing factor to the overuse of extended-spectrum antibiotics (ESA) for CAP is that the causative pathogen is unknown in nearly half of cases, and initial treatment is almost always empiric [4, 5]. Guidelines of the American Thoracic Society and Infectious Diseases Society of America (ATS/IDSA) recommend limiting ESA to inpatients with risk factors for resistant pathogens, but many inpatients with CAP receive ESA, often throughout their hospital stay [6–8].

An accurate pathogenic diagnosis can contribute to antimicrobial stewardship in 2 ways: (1) by allowing for initial narrow-spectrum therapy and (2) by providing confidence when de-escalating therapy following negative cultures. However, without a diagnostic test, many clinicians are uncomfortable with de-escalation, fearing an undiagnosed resistant pathogen could cause treatment failure. Rapid molecular diagnostic assays have the potential to identify causative pathogens, but they are rarely part of the diagnostic work-up, and results are often ignored [9, 10]. In a national sample of patients with CAP from 177 US hospitals, we found that only 16% had a pneumococcal urinary antigen testing (UAT) performed and < 25% were tested for respiratory viruses [11, 12]. Both the ATS/IDSA CAP guidelines and the antimicrobial stewardship implementation guidelines recommend routine testing of inpatients for influenza during influenza activity; neither one recommends routine UAT testing [6, 13]. Both sets of recommendations are based on limited evidence and it is not known whether widespread testing for viruses would reduce antibiotic use. In a multi-hospital dataset, we found that patients who tested positive for respiratory viruses received 0.8 fewer days of antibiotics, and patients who tested positive with UAT were twice as likely to have their ESA de-escalated by hospital day 3 [11, 12]. There is therefore a need for large, randomized trials that can evaluate the impact of initial diagnostic testing on antibiotic prescribing and patient outcomes.

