De-escalation following negative bacterial cultures is another antimicrobial stewardship target. While most de-escalation follows the identification of a susceptible pathogen, the IDSA/ATS guidelines also recommend de-escalation to a narrower spectrum at 48 h if cultures are negative [6]. However, this recommendation is based on observational studies. In our study of 164 US hospitals, we found that de-escalation practices following negative cultures varied widely by hospital, and no hospital de-escalated even 40% of eligible patients [14]. De-escalation was associated with shorter length of stay and lower rates of inpatient mortality. A hospital-wide pharmacist-led effort to encourage physicians to follow the ATS/IDSA guidelines and de-escalate after 48 h could help overcome fears about resistant pathogens and treatment failure.

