### Interim analyses

Safety interim analysis will be conducted every 6 months. The all-cause death incidence rate within the first 30 days of admission is calculated as the number of all-cause deaths divided by the number of eligible patients (according to inclusion and exclusion criteria) and expressed per 1000 (or 10,000 patients) per 30 days of follow-up. We will use the all-cause death incidence rate within the first 30 days of admission calculated during the 1-year period before the study onset as a baseline estimation. We will calculate incidence-rate ratios and incidence-rate differences between the four treatment groups, using the usual care group as the reference. The four treatment arms are rapid testing and de-escalation, rapid testing only, de-escalation only, and usual care (neither rapid testing nor de-escalation). If the all-cause death incidence-rate ratio or incidence-rate difference between the usual care group and any of the three intervention groups is statistically significant at a *p*-value < 0.05, the study’s Steering Committee will be notified.

Futility interim analysis will be conducted after half the data have been collected (patient *n* = 6250). At that time, we will calculate conditional power: the probability of statistical significance at the study’s completion given the date obtained so far. We will calculate the futility index as 1 − conditional power. The study will be stopped if the futility index is above 0.8 (conditional power falls below 0.2). To calculate conditional power, we will calculate current (at *n* ≥ 6250) z-statistic, using the PASS Probability Calculator. PASS 2022 implemented conditional power calculation using Jennison and Turnbull (year 2000; pages 205–208), the general upper one-sided conditional power at stage k for rejecting a null hypothesis about a parameter θ at the end of the study, given the observed test statistic, *Z*_*k*_.

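### Intervention-related unanticipated problems can reach the IRB later than major deviations, and the only scheduled safety analysis names death alone

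*Protocol article*

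**What the plan says.** Assessment of safety sets two IRB timelines in adjacent sentences. For problems arising from the intervention: "Unanticipated problems related to the intervention will be logged and reported to the Institutional Review Board (IRB) at the time of continuing renewal". For protocol departures: "Major deviations will be reported to the IRB upon discovery". The renewal interval is not given, and no exception is made for serious or recurring problems. The same section lists things the study team will do periodically, among them protecting participants, resolving centre problems and running an interim analysis if appropriate. It attaches no interval, outcome or trigger to that list.

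Interim analyses then fixes one recurring review: "Safety interim analysis will be conducted every 6 months". The outcome it defines is mortality: "The all-cause death incidence rate within the first 30 days of admission is calculated as the number of all-cause deaths". The denominator is every eligible patient. If an intervention group differs from usual care at p < 0.05, the stated consequence is "Steering Committee will be notified".

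Background and rationale explains clinicians' reluctance to de-escalate as "fearing an undiagnosed resistant pathogen could cause treatment failure", and says a pharmacist-led effort "could help overcome fears about resistant pathogens and treatment failure". Outcomes lists ICU transfer more than 24 h after admission, empyema and re-escalation to extended-spectrum antibiotics (ESA) as secondary outcomes. Data collection and quality check says EMR data, including the outcomes, are extracted periodically.

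**The concern.** There are two separate gaps.

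The first is the order of urgency. A problem already attributed to the intervention waits for renewal, while a major deviation does not. Both interventions depend on automated steps (orders appended by decision support, and a patient list generated by an algorithm), so a fault could repeat across patients and hospitals before the IRB hears of it.

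The second is the content of the scheduled review. De-escalation is recommended only for clinically stable patients with negative cultures after 48 h, but the mortality rate is taken over all eligible patients. A rise in non-fatal failures among the patients actually reached could leave that rate almost unchanged and trigger nothing.

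Both matter more than usual because the trial runs under a waiver of consent, justified by minimal risk, and patients cannot practicably opt out.

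**Working it through.** The plan states no figure for this point, so the check is a comparison of the text followed by arithmetic for scale.

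**Text comparison**

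| Event | Who is told | When | Source |
|---|---|---|---|
| Unanticipated problem related to the intervention | IRB | Continuing renewal, interval not stated | Assessment of safety |
| Major deviation | IRB | On discovery | Assessment of safety |
| Mortality difference at p < 0.05 | Steering Committee | 6-monthly analysis | Interim analyses |
| ICU transfer after 24 h, empyema, re-escalation | No recipient stated during the trial | No interim date stated | Outcomes; Interim analyses |

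The first two rows show the inversion. The last two show that the dated review covers only death. The two gaps do not fill each other: treatment failure is foreseen in the rationale, so it may not count as an unanticipated problem at all. Its gap therefore rests on the Interim analyses section alone.

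**Patients admitted between reports**

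Inputs: 12,000 patients (Sample size and power analysis); enrolment from November 2022, trial end November 2025 (Trial status). Enrolment is taken as 36 months, or 30 months if the last 6 are follow-up only.

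- Monthly accrual: 12,000 / 36 = 333; 12,000 / 30 = 400.
- Per 6 months: 6 × 333 = 2,000 to 6 × 400 = 2,400. With four equal arms this is 500 to 600 per arm.
- Per 12 months, if renewal is yearly (assumption): 4,000 to 4,800.
- At the six de-escalation hospitals (half of 12): 2,000 to 2,400 of these.

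**What the mortality trigger can detect**

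Two-proportion normal test of one arm against usual care, two-sided 0.05, 80% power, base rates of 5% and 8% assumed, clustering ignored:

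power = Φ{[d − 1.96·√(2p̄(1−p̄)/n)] / √[(p₁(1−p₁) + p₂(1−p₂))/n]}, where d = p₂ − p₁ and p̄ is the mean of p₁ and p₂.

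At n = 500 per arm, 5% v 9.6%: d = 0.046, p̄ = 0.073, null SE 0.01645, alternative SE 0.01639. This gives (0.046 − 0.03225) / 0.01639 = 0.84, power 80%. Solving the same formula for other sizes:

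| Patients per arm | From 5% to | From 8% to |
|---|---|---|
| 500 (first look) | 9.6% | 13.5% |
| 1,000 | 8.1% | 11.7% |
| 1,500 | 7.5% | 11.0% |
| 2,500 | 6.9% | 10.3% |
| 3,000 (full sample) | 6.7% | 10.1% |

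The rows after the first apply only if looks are cumulative, which the article does not state. Allowing for clustering, with three hospitals per arm, would make every detectable rise larger. The table describes the sensitivity of the death trigger; it says nothing about the size of any non-fatal signal.

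**The case against.** A reader might infer that non-fatal treatment failure has no timely route to anyone who can act, or that nobody looks at these outcomes before the end. The documents do not support either. Problems are logged, and the study team has a periodic duty to protect participants, resolve problems and run further interim analysis if it sees fit. A pharmacist audits the alerts on weekdays, site champions are in place, and the treating physician can override any order or recommendation. The article is silent on whether non-fatal outcomes are looked at; it does not say that they are not. What stands is narrower: no timed trial-level review of them is specified.

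Two further limits are fair. Only major deviations are expedited, and neither category is defined, so a serious list or alert fault might itself be classed as a major deviation and reported at once. And the protocol presents treatment failure as a clinicians' fear while calling the interventions minimal risk; it does not declare treatment failure an expected harm of the trial.

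It can also be said that an article leaves the contents of monitoring tables to a fuller document. That has some force for the added outcomes, which are therefore a recommendation. It does not touch the reporting order, which the article states outright. Nor does physician override answer the point, since a clinician treating one patient cannot see a difference between arms or a fault repeated across hospitals.

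**Conclusion.** The point holds in two parts. As written, intervention-related unanticipated problems can reach the IRB later than major deviations. Separately, the one scheduled safety analysis names only 30-day all-cause death, and no timed trial-level review is specified for non-fatal failure markers that are already collected.

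The length of the IRB delay is unknown because the renewal interval is not stated; the 4,000 to 4,800 patients between reports rest on yearly renewal and 30 to 36 months of enrolment. The detectable rises of 5% to 9.6% and 8% to 13.5% rest on assumed base rates, apply only to a first look of about 500 per arm, ignore clustering, and shrink if later looks are cumulative. Neither part affects the primary analysis or the sample size. This is an inexpensive improvement in oversight that should be made; it is not evidence that patients are unprotected.

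**What to change.** In Assessment of safety, state that unanticipated problems related to the intervention are reported to the IRB and the Steering Committee on the same timeline as major deviations.

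In Interim analyses, add three descriptive rows by arm to the 6-monthly tables for the Steering Committee: ICU transfer more than 24 h after admission, empyema, and re-escalation to ESA. Show re-escalation over all eligible patients as well as over those de-escalated. The intervention changes who is de-escalated, so the second denominator alone is not comparable between arms.

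The cost is an amendment of a few sentences and three rows built from outcomes already extracted. The downside is a few extra reports and some chance signals for the Steering Committee to judge, which is why the rows should be descriptive and carry no test or threshold.

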### Interim analyses

Safety interim analysis will be conducted every 6 months. The all-cause death incidence rate within the first 30 days of admission is calculated as the number of all-cause deaths divided by the number of eligible patients (according to inclusion and exclusion criteria) and expressed per 1000 (or 10,000 patients) per 30 days of follow-up. We will use the all-cause death incidence rate within the first 30 days of admission calculated during the 1-year period before the study onset as a baseline estimation. We will calculate incidence-rate ratios and incidence-rate differences between the four treatment groups, using the usual care group as the reference. The four treatment arms are rapid testing and de-escalation, rapid testing only, de-escalation only, and usual care (neither rapid testing nor de-escalation). If the all-cause death incidence-rate ratio or incidence-rate difference between the usual care group and any of the three intervention groups is statistically significant at a *p*-value < 0.05, the study’s Steering Committee will be notified.

Futility interim analysis will be conducted after half the data have been collected (patient *n* = 6250). At that time, we will calculate conditional power: the probability of statistical significance at the study’s completion given the date obtained so far. We will calculate the futility index as 1 − conditional power. The study will be stopped if the futility index is above 0.8 (conditional power falls below 0.2). To calculate conditional power, we will calculate current (at *n* ≥ 6250) z-statistic, using the PASS Probability Calculator. PASS 2022 implemented conditional power calculation using Jennison and Turnbull (year 2000; pages 205–208), the general upper one-sided conditional power at stage k for rejecting a null hypothesis about a parameter θ at the end of the study, given the observed test statistic, *Z*_*k*_.

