### Participating sites

Enrolling sites will include ten hospitals in Northeast Ohio (Cleveland Clinic Main Campus, Fairview Hospital, Hillcrest Hospital, Marymount Hospital, Akron General Hospital, Avon Hospital, Euclid Hospital, Lutheran Hospital, Medina Hospital, and South Pointe Hospital) and two from Florida (Weston and Indian River Hospital) (Table 2). Hospitals will be divided into 3 strata based on teaching status, size of the hospital, and number of CAP patients with each stratum containing 4 hospitals. The hospitals will then be randomized to each of the 4 trial arms with an effective sample size of 3 hospitals in each arm.

**Table 2 Tab2:** Enrolling hospital sites by bed size and teaching status

Hospital	Number of beds	Residency program
Cleveland Clinic Main Campus	1167	Yes
Fairview General Hospital	488	Yes
Hillcrest Hospital	341	No
Marymount Hospital	195	No
Akron General	532	Yes
Avon Hospital	126	No
Euclid Hospital	110	No
Lutheran Hospital	119	Yes
Medina Hospital	148	No
South Pointe Hospital	167	Yes
Cleveland Clinic Florida, Weston Hospital	230	Yes
Indian River Hospital	332	No

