Secondary outcomes:Within 48 h of admission:Viral testing ordered (yes/no): Proportion of patients for whom viral testing was ordered. We will analyze each virus individually as well as all viruses combined (i.e., any viral testing).Proportion of patients testing positive for influenza within 48 hDetection of RSV (yes/no): Proportion of patients testing positive for RSVDetection of viruses/other CAP pathogens (yes/no): Proportion of patients testing positive for each of the viruses/other CAP pathogensTreatment with anti-viral medications (oseltamivir, zanamivir, peramivir, baloxavir, ribavirin, remdesivir, nirmatrelvir, COVID-19 medications) (yes/no)Proportion of patients for whom *S. pneumoniae* urinary antigen test (UAT) is performed.Proportion of patients with a positive pneumococcal UAT.Treatment with antiviral medications (oseltamivir, zanamivir, peramivir, baloxavir, ribavirin, remdesivir, nirmatrelvir, COVID-19 medications) within 21 daysDe-escalation of ESA within 72 h from admission (yes/no) — Proportion of patients whose ESA (imipenem, meropenem, piperacillin-tazobactam, aztreonam, cefepime, ceftazidime, tobramycin, ceftazidime-avibactam, ceftolozane-tazobactam, meropenem-vaborbactam, imipenem-cilastatin-relebactam, cefiderocol, ceftaroline, tigecycline, eravacycline, amikacin, linezolid, or vancomycin) are de-escalated within 72 h from admission.Re-escalation to ESA after de-escalation (yes/no) within 21 days from admission. Proportion of patients whose antibiotics were de-escalated and that were subsequently re-escalated to ESA (imipenem, meropenem, piperacillin-tazobactam, aztreonam, cefepime, ceftazidime, tobramycin, linezolid or vancomycin).Total duration of any antibacterial antibiotic within 21 days. Total duration of any antibacterial antibiotic treatment up to 21 days, including re-initiation of antibiotics.Fourteen-day mortality. Patient’s vital status will be ascertained from the EHR if available, otherwise from the Ohio State Death Index.Thirty-day mortality.ICU transfer after admission (> 24 h after admission): Proportion of patients transferred to the ICU > 24 h after admission up to 21 days.Healthcare-associated *Clostridioides difficile* infection (CDI) (yes/no) — CDI after 72 h of admission: Proportion of patients with CDI after 72 h of admission until 30 days.Acute kidney injury (AKI) after 48 h within 21 days (yes/no): Proportion of patients with AKI after 48 h of admission. AKI will be defined as an increase in serum creatinine ≥ 0.3 mg/dl within 48 h or an increase > 1.5 times baseline [16].Total inpatient cost (from the hospital’s cost accounting system): From admission to discharge or 21 days, whichever comes first.Hospital length-of-stay (days, hours) — length of stay will be calculated as whole days from the time of admission to the time of discharge.Empyema (yes/no) — after 48 h, within 21 daysThirty-day readmission (yes/no)Infection with a resistant organism in the future (yes/no) within 6 months after discharge. Resistance to CAP therapy will be defined as resistance to either a respiratory quinolone or to both a beta-lactam/3rd generation cephalosporin and a macrolide. Multi-drug resistance will be defined as any CAP bacterial isolate that tests either intermediate (I) or resistant (R) to at least one agent in three or more antimicrobial classes.

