## Statistical methods

### Data analysis plan

The data analysis will be conducted following the intention-to-treat (ITT) principle which includes 3 rules. The first rule establishes the landmark event for entry into the study, which is the randomization of hospitals. All randomized hospitals will be considered enrolled, and data of eligible patients treated by enrolled hospitals will be analyzed. The second rule establishes patient-level data collection, which is independent of treatment assignment. The third rule defines the pre-specified time period for counting study events, which varies for each outcome.

We will follow the order principle of analyses, which states that analyses involving the primary outcome measure must be preceded by analyses of higher-order outcomes when those outcomes are censored. In our study, all-cause death events are censored. To follow the order principle of analyses, we will compare the all-cause mortality incidence rate within the first 30 days of admission across the four treatment groups. Incidence rate is calculated as the number of all-cause deaths divided by the number of included patients and expressed per 1000 (or 10,000 patients) per 30 days of follow-up. We will calculate the incidence-rate difference between the four treatment groups, using the usual care group as the reference. The four treatment arms are rapid testing and de-escalation, rapid testing only, de-escalation only, and usual care (i.e., neither rapid testing nor de-escalation).

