To address the non-adherence limitation, we will conduct two secondary analyses [17]. First, we will perform an as-treated analysis, comparing outcomes among those who receive the treatment versus those who receive control, regardless of randomization. Second, we will calculate complier average causal effect (CACE) estimation, which uses randomization as an instrument to account for unobserved confounding and provides a randomization-respecting estimate [18]. CACE estimates the intention-to-treat effect in the subgroup of participants who always comply with their treatment allocation. In addition, we will use per-protocol analysis, comparing those who comply with their random allocation in the treatment group with all the controls. We will use an inverse probability weighting approach to minimize selection bias [19]. All the secondary analyses will use the framework of mixed-effects (hierarchical, two-level) models as described above for the primary ITT analyses.

All continuous secondary outcomes will be analyzed using the same method as the primary outcome. For each secondary outcome, we will adjust for the rate of that outcome in the 12 months prior to the study. Binary outcomes will be analyzed using generalized linear mixed-effects models. All analyses will be conducted using SAS 9.3 (Cary, NC), R-studio (Boston, MA), and STATA (College Station, TX). Our trial will follow the Consolidated Standards of Reporting Trials guidelines, extended for cluster-randomized controlled trials [20].

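### The mortality safety trigger and the mortality comparison that precedes the primary analysis are defined on crude rates with no clustering term, and no death source is named for the two Florida hospitals

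*Protocol article*

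**What the plan says.** **Interim analyses.** The 30-day death rate is "calculated as the number of all-cause deaths divided by the number of eligible patients (according to inclusion and exclusion criteria"). Rate ratios and differences are formed for each of three intervention arms against usual care every six months. The rate from the year before the study serves as a baseline estimate. The action rule reads "If the all-cause death incidence-rate ratio or incidence-rate difference between the usual care group and any of the three intervention groups is statistically significant" at p < 0.05, the "Steering Committee will be notified". No test is named, and no allowance for repeated looks or for three comparisons is stated.

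**Data analysis plan.** Before the primary outcome is analysed, 30-day mortality is compared across the four arms: "Incidence rate is calculated as the number of all-cause deaths divided by the number of included patients". This paragraph gives rate differences against usual care and no significance threshold of its own. Later the same section says "Binary outcomes will be analyzed using generalized linear mixed-effects models", with adjustment for the outcome's rate in the prior 12 months. Thirty-day mortality is listed under Outcomes as a secondary outcome, so that model covers it too.

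**Death ascertainment.** Under Outcomes, beside 14-day mortality, "vital status will be ascertained from the EHR if available, otherwise from the Ohio State Death Index". The Discussion adds other registries within the health system. Participating sites lists ten Ohio hospitals and "two from Florida (Weston and Indian River Hospital"). The Abstract calls 14-day mortality in-hospital; Outcomes does not.

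**The concern.** Patients in one hospital share case mix, discharge practice and staff, so a three-against-three hospital comparison carries between-hospital variation that a crude comparison of proportions does not see. The plan recognises this elsewhere: in the random intercept for the primary outcome, in the mixed model for binary outcomes, and in the ICCs of the sample size section. The two mortality comparisons defined on crude rates are the exception. The same endpoint therefore has two described analyses that can disagree.

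Ascertainment is a separate matter. Two hospitals can fall in at most two of the four arms. If post-discharge deaths are traced less fully there, the under-count differs by arm. The Discussion hopes to demonstrate that de-escalation is safe, and 30-day mortality bears directly on that.

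**Working it through.** **Inputs from the protocol.** 3 hospitals per arm (Participating sites); mean 1000 patients per hospital, coefficient of variation 0.4; ICC 0.001 for Aim 1 and 0.005 for Aim 2, the latter also applied to *C. difficile* infection and kidney injury (Sample size and power analysis). Looks every 6 months; enrolment from November 2022 to a planned end in November 2025, about 36 months, so 6 looks, or 5 if the last coincides with the end. **Assumed:** 30-day mortality 5–10%; the planning ICCs stand in for mortality, for which none is given.

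**1. Reproduce the plan's own figure.** Design effect DE = 1 + [(1 + 0.4²) × 1000 − 1] × 0.001 = 1 + 1159 × 0.001 = 2.159. For Aim 1, SE = 3.5 × √(2 × 2.159 / 6000) = 0.0939 and 0.3 / 0.0939 = 3.20. Noncentral t with 10 df gives 82.1% power, against 83% stated. The clustering inputs are therefore read correctly.

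**2. True size of one unadjusted comparison at full size.** Size = 2 × [1 − Φ(1.96 / √DE)].
- ICC 0.001: DE = 2.159; 1.96 / 1.469 = 1.334; size 18.2%.
- ICC 0.005: DE = 1 + 1159 × 0.005 = 6.795; 1.96 / 2.607 = 0.752; size 45.2%.

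**3. All looks and comparisons, no true effect.** Beta-binomial simulation, pooled two-proportion z-test, each arm against usual care. The lower figure is for 5 looks and equal hospitals, the higher for 6 looks and unequal hospitals.

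| ICC | At least one p < 0.05 |
|---|---|
| 0 | 33–36% |
| 0.001 | 51–58% |
| 0.005 | 81–86% |

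With 5 looks, a false signal of harm occurs in about 16%, 26% and 44% of trials. Results barely differ between 5% and 10% mortality. The first row is due to repeated looks and three comparisons alone.

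**4. What a clustered test gives up.** Smallest flagged difference with 3000 against 3000 patients at 5% mortality: SE = √(2 × 0.05 × 0.95 / 3000) = 0.563 points.
- Unadjusted: 1.96 × 0.563 = 1.1 points.
- Times √DE: 1.6 points (ICC 0.001) or 2.9 (ICC 0.005).
- With t on 4 df (2.776 in place of 1.96): 2.3 or 4.1 points.

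**5. Florida under-count.** With equal hospital sizes and a share x of 30-day deaths missed in one of an arm's three hospitals, the observed rate ratio with no true effect is (3 − x) / 3:
- x = 10%: 0.97
- x = 25%: 0.92
- x = 50%: 0.83

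If that hospital is in usual care, a given intervention arm is falsely flagged as harmful in about 5–6%, 12–20% and 35–57% of trials respectively (one full-size look, no clustering, mortality 5–10%), against 2.5% nominal.

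**The case against.** **No test is named.** That the comparison ignores clustering is inferred from how the rate is defined, and a variance method may sit in a fuller document. This stands as a limit on the claim. What the article does state is a crude rate with a p-value rule in one place and a mixed model for the same endpoint in another, with nothing tying them together.

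**Baseline mortality is used.** A reader might infer that the plan disregards it. The text does not support that: prior-year mortality appears as an interim baseline estimate and as an adjustment for secondary outcomes. It is only not linked to the significance rule. If prior-year deaths were traced in the same way, that adjustment could also absorb part of a stable Florida under-count, but only in the mixed model.

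**A sensitive alarm is defensible.** It triggers notification, not stopping, and step 4 shows that a clustered test needs a clearly larger excess before it fires. This is why the crude rates should be kept as descriptive monitoring.

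**Clustering is not the whole story.** A reader might infer that most alarms would reflect hospital differences. At ICC 0.001 the larger part of the alarm rate is present without any clustering; only near ICC 0.005 does clustering dominate.

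**The Ohio index is not the only source.** The EHR comes first and is shared by all hospitals, and the Discussion allows other registries. Florida in-hospital deaths and later deaths recorded in the EHR are captured. The under-count concerns the remaining post-discharge deaths.

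**Conclusion.** The point holds with limits. As written, the trigger and the preceding mortality comparison rest on crude three-against-three rates. An unadjusted test would have a true size of about 18–45% for one full-size comparison at the plan's own ICCs. Over the whole trial, chance alarms would range from about a third of trials without clustering to more than four fifths at ICC 0.005. Repeated looks and three comparisons contribute as well as clustering. These figures assume that planning ICCs for other outcomes apply to mortality, and the simulation ignores the stratified allocation, which could lower them.

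Post-discharge deaths missing from the EHR are likely under-counted at the two Florida hospitals. This masks harm if such a hospital is in an intervention arm and falsely suggests harm if it is in usual care. A reader might infer a bias in favour of the interventions, but the allocation is not shown, so the direction is open. The size is open too: 50% missed is an illustration, not an estimate. The problem applies mainly to 30-day mortality; 14-day mortality escapes it if the Abstract's in-hospital definition holds.

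**What to change.** **Analysis.**
- Base the mortality comparison in the Data analysis plan, and the p-value in the notification rule, on the mixed model already given for binary outcomes with prior-year mortality, or on a hospital-level test. Use a small-sample correction for 12 clusters in either case.
- State how the repeated looks and the three comparisons are treated; a clustered test alone leaves that part of the chance alarms in place.
- Keep reporting the crude rates to the Steering Committee as descriptive monitoring, without a significance label.

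**Ascertainment.**
- Name a Florida or national death source for the two Florida sites.
- Reconcile the sources given under Outcomes and in the Discussion, and the two descriptions of 14-day mortality.
- Report 30-day mortality also for the ten Ohio hospitals alone.

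**Cost.** Revised wording, a records request with a small fee, and a formal trigger that is less sensitive to a true excess of deaths, which the descriptive monitoring partly offsets.
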